#### **B. Weekly Calendars**

Weekly online calendars will be used to assess:

- Physical activity both related to the study and other planned activities
- Falls adverse events
- Falls and injuries
- Mobility
- Fatigue
- Exercise Adherence both related to the study and other planned activities
- Health services use

Reported falls will be followed up with a phone call to assess severity and ensure ongoing participant safety.

### **xi. Follow-up assessment (T2)**

After each 12 weeks ( $\pm 2$  weeks), participants in all groups across all centers will undergo another *functional assessment*, including measurement of clinical outcomes and a gait analysis

during which EEG, EMG and kinematics data will be collected. As done at T0 and T1 a video scan of the participants head will be taken to determine the electrode position.

## **A. Functional assessment**

### *Clinical assessments*

We will assess changes in functional mobility with the standard timed-up-and-go (TUG) test and the 2-minute walk test, balance and fall risk with the MiniBESTest, and motor symptoms of PD with the MDS-UPDRS, cognition using the MoCA and CTT. We will use questionnaires to assess effects on gait self-efficacy (modified gait efficacy scale, mGES and falls efficacy scale international, FES-i) fatigue (FACIT-F) and health-related quality of life (EQ-5D). After the 2-minute walk test self-rated walking quality and mental effort to walk will be assessed using visual analogue scales.

### *Kinematic and neurophysiological measures*

We will assess preferred gait speed and maximal gait speed using a 20-m walk test (Primary outcome).

Participants start walking on the treadmill for 7 minutes for familiarization. After that, they will then walk at their preferred speed for 5 minutes, to assess the secondary outcomes, step-width and stride-time and the variance of these parameters, from data of at least 100 strides. The fixed 1.4 km/h is attainable for an estimated 95% of patients with moderate PD. However, for those who cannot attain 1.4 km/h at T0, their preferred walking speed T0 will be their fixed speed during all functional assessments. The treadmill assessment will be repeated at their preferred speed. Additionally, during Treadmill walking data from the EEG and EMG will be collected to derive beta-band power in motor areas and calculate cortico-muscular coherence (CMC) between brain and muscle activity.

### *Qualitative interviews*

To meet the JPND grant guidelines, which includes a focus on recording end-user experiences participants, in-person or remote/telephone structured interview at T2 will be performed on enrolled participants. Answers to the open-ended questions (as detailed in the interview guide) will be analysed using qualitative methods to understand the participants' experiences, enablers and barriers to intervention success. The planned number of participants necessary to be interviewed at each site for each arm in order to achieve saturation is as follows:

- 20 people from SDTT (5 each from Sydney, Keil, Bologna and Tel Aviv)
- 10 people from SDTT + VR (5 each from Bologna and Tel Aviv)
- 10 people from SDTT + MP (Kiel)
- 10 people from SDTT + VR + MP (Sydney)

These will provide data for qualitative analyses of both cultural context and intervention type differences. Interim qualitative analyses will be performed at monthly intervals in order to check whether saturation is achieved.

Online questionnaires will be used to assess:

- System usability
- Physical Activity Enjoyment

- Exercise Self Efficacy
- Barriers and Enablers to long term use

Furthermore, space for participants to provide feedback and suggestions for future improvements will be used to record all participants' experiences of the home-based walk training.

## **B. Home assessment**

A home assessment visit for the period of at least 7 days should be completed. Participants will wear inertial measurement units (IMUs), either a single unit on the lower back or, in a subgroup, a three-sensor system, to continuously record motion data. The sensor on the lower back will be attached using medical tape, while the ankle sensors will be fastened using a self-adjustable band to ensure participant comfort. The sensors can be removed quickly and can be easily repositioned following the instructions provided. The planned number of participants to wear the 3-sensor setup at each site for each interventions follows:

- i. 20 people from SDTT (5 each from Sydney, Kiel, Bologna and Tel Aviv)
- ii. 16 people from SDTT + VR (8 each from Bologna and Tel Aviv)
- iii. 8 people from SDTT + MP (Kiel)
- iv. 8 people from SDTT + VR + MP (Sydney)

Participants will be chosen in order of participation until the minimum sample size required is reached.

Participants will be asked to complete a daily diary via their personal smartphone or by paper pencil depending on their preference, including the following information: medication intake, physical activities performed, freezing of gait (FOG) episodes, falls experienced and information on fatigue. Other than the clinical assessment, that is performed during ON medication, the home assessment contains periods of ON, OFF, and transitions between phases, along with various contextual factors that influence mobility. To accurately evaluate the relationship between improvements in lab-based and daily-life gait outcomes, this diary records the influence of Parkinson's medication and physical activity on mobility during the home assessment and ensures with that comparability between the gait outcomes of T0 and T1. During the functional assessment, participants receive support in personalizing the diary by entering their medication schedule and adding typical physical activities. Over seven days, the diary is completed daily and is expected to take 1–3 minutes per day. Only deviations from the medication schedule need to be noted, while normal intake can simply be checked off for each day. Physical activities, FOG episodes, and falls can be logged by adding abbreviations/X marks in the provided timetable. Participants are encouraged to keep the diary beside their medication box to help prevent late entries, while no daily reminders will be sent to minimize the burden on participants.

## **xii. Outcome variables**

The following outcome variables will be collected. For an easier overview clinical assessment has been collectively referred to outcomes A-E.

## **A. Descriptive Measures**

- A1. General descriptive measures: Year of birth, gender, height, weight, shoe size, education, employment, living arrangement, current physical or other therapies, smoking history, alcohol consumption at To.
- A2. Treatment acceptance and satisfaction to the training and overall protocol will be assessed to T1 and T2.

## **B. Clinical outcome measures**

- B1. Fall events (occurrence and frequency) and fall related injuries: The number of falls and whether the falls were injurious will be recorded. Twelve-month retrospective during To and during the duration of the trial.
- B2. Fracture history: Number and type of fracture sustained will be recorded. Twelve-month retrospective during To.
- B3. Medication: Current medication will be recorded at each visit.
- B4. Euro-Qol (EQ-5D): The EQ-5D measures quality of life. It consists of two components; health state description and evaluation. This will be completed on To, T1 and T2.
- B5. Frailty Index (FI): The FI measures frailty five different criteria (shrinking, low physical endurance/energy, low physical activity, weakness and slow walking speed). This will be completed at To, T1 and T2.
- B6. Functional Assessment of Chronic Illness Therapy (FACIT) Fatigue scale: The FACIT Fatigue Scale measures fatigue during usual daily activities over the past week. This will be completed at To, T1 and T2.
- B7. Visual Analogue Scale (VAS): The VAS will be used to determine the pain during rest and walking and the self-assessed quality of walking. This will be completed at To, T1 and T2.
- B8. Groll Functional Comorbidity Index (FCI): This is a self-administered test with physical function as the outcome. This will be completed at To.

## **D. Neuropsychological measures**

- D1. Short Falls Efficacy Scale International (Short FES-i): The short FES-i is a measure the level of concern about falling during social and physical activities inside and outside the home. This will be completed at To, T1 and T2.

- D2. Montreal Cognitive Assessment (MoCA): The MoCA is a measure of cognitive impairment. It assesses different cognitive domains: attention and concentration, executive functions, memory, language, visuo-constructional skills, conceptual thinking, calculations, and orientation. This will be completed at T0 and T2.
- D3. Color Trail Test (CTT): Color Trail Test  is a neuropsychological assessment that assesses a person's cognitive flexibility, visual scanning and executive function. It involves connecting a series of numbered circles, alternating between numbers and letters in ascending order as quickly as possible, and provides insight into attention, mental flexibility and processing speed. This will be completed at T0 and T2.

## **E. Parkinson-Specific Assessments**

- E1. Movement Disorder Society Unified Parkinson's Disease Rating Scale (MDS-UPDRS): The MDS-UPDRS describes disease progression. It is separated into four different domains including cognitive function, behaviour and mood, activities of daily living (ADL) and motor examination. This will be completed at T0, T1 and T2.
- E2. New Freezing of Gait Questionnaire (NFOGQ): The NFOGQ is a tool to detect and evaluate the impact and severity of freezing of gait. This will be completed at T0, T1 and T2.

## **F. Kinematics and Neurophysiological measures**

- F1. Kinematics: 3D motion capture data will be recorded at T0, T1 and T2.
- F2. Electroencephalography (EEG): EEG records an electrical signal from the surface of the scalp and can be used to describe brain activity. This will be recorded at T0, T1 and T2.
- F3. Electromyography (EMG): Surface EMG records the electrical activity of superficial muscles through electrodes placed on the skin, and it is commonly used in clinical and research settings to assess muscle function, fatigue, and activation patterns. This will be recorded at T0, T1 and T2.

## **G. Home assessment**

- G1. The steps per day will be recorded at T0 and T1.
- G2. The amount and length of uninterrupted walk durations will be determined (T0 & T1)
- G3. The stride time variability will be derived at T0 and T1.
- G4. Symmetry of gait will be determined at T0 and T1.
- G5. FOG episodes, Medication and Physical activity will be recorded by self-reports (T0 and T1)
- G6. Weekly Calendars will be used to assess Physical activity, Falls and Injurious Falls.

## **H. Engagement and Process Outcomes (T1 and T2)**

- H1. Acceptability and satisfaction with the intervention will be assessed with the 10-item System Usability Scale, Physical Activity Enjoyment Scale (PACES) and questions developed specifically for the components of this study.
- H2. Changes in attitudes towards physical activity will be assessed with the Exercise Self-Efficacy Scale (ESES)
- H3. Exit interviews will be conducted at T2 to explore the barriers and enablers to long-term use and reasons for ceased involvement (if applicable) using pre-prepared, open-ended questions according to qualitative interviews methods .

### **xiii. Safety and risk management procedures**

Clinical treadmill training with a harness is considered a safe and effective intervention for patients with Parkinson's disease (PD). The use of a harness provides additional support and

reduces the risk of falls during treadmill training, allowing patients to focus on their gait and balance training without fear of injury. In this respect, during the intervention, the risk of adverse events is not increased compared to what may be expected during regular daily life activities. Clinical treadmill training with a harness is a safe and effective intervention that can improve the physical and functional abilities of patients with PD.

Falls, falls-related injuries, myalgia and fatigue are considered potentially trial-associated adverse events (AE) and will thus be monitored for the duration of the trial. We will assess the number of falls and the number of injurious falls during the previous 12-months at To, throughout the duration of the trial and the weeks preceding T2.

An AE form should be completed and returned to the local Principal Investigator within 24 hours of the site's awareness of the event. This form must be reviewed and signed off by the PI will determine the seriousness and causality in conjunction with the trial procedures.

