|                      | Local divergence exponent
Foot placement model (multiple linear regression) : 
 
- Relative explained variance (<math>R^2</math>)
 
- Standard deviation of residual (i.e. foot placement error)
 
- Regression coefficients
 
                                                                                                                                                                                     | Kinematics                             |
|                      | Beta-band Power in motor areas
Cortico-muscular coherence                                                                                                                                                                                                                                                                                                                                                                                                                     | Neurophysiological                     |
|                      | Steps per day
Amount and length of uninterrupted walk durations
Stride time variability
Symmetry                                                                                                                                                                                                                                                                                                                                                                        | Home assessment                        |
|                      | Adverse events
Falls and injuries
Mobility
Fatigue
Exercise Adherence
Health services use                                                                                                                                                                                                                                                                                                                                                                         | Weekly Calendars and Safety Monitoring |

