After each session, the self-rated walking quality and mental effort visual analogue scales will be recorded and used to track progression and help guide the supervising clinician in tailoring the difficulty of subsequent sessions.

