### **x. Maintenance Period (T1 to T2)**

#### **A. Home-based walking**

All participants will be offered a home-based speed dependent walk training intervention. This intervention is an App based training for gait adaptability and allows users to set their own training time and pace. It delivers a rhythmic metronomic beat for three different walking speeds, designed to trigger movement and encourage better walking patterns. The Walking Tall app can be installed on iOS and Android devices and does not store any personalized data. During the maintenance period, participants will be supported using the app to progress towards World Health Organisation recommendations for moderate intensity exercise through a personalised goal setting session.

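### Falls, injuries and myalgia are to be monitored throughout the trial, but no prompted tool for them is clearly scheduled during training, the only period when the arms differ

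*Protocol*

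**What the plan says.** Section 5.xiii (Safety and risk management procedures) makes the commitment: "Falls, falls-related injuries, myalgia and fatigue are considered potentially trial-associated adverse events (AE) and will thus be monitored for the duration of the trial". Its next sentence repeats it for falls and injurious falls. Item B1 in section 5.xii.B says the same of falls, "Twelve-month retrospective during To and during the duration of the trial", but names no instrument for the part after T0.

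The weekly calendar is described in section 5.x, whose heading begins "Maintenance Period (T1 to T2". There, "Weekly online calendars will be used to assess" introduces a list covering activity, falls and injuries, mobility, fatigue, adherence and health services use, with one entry reading "Falls adverse events". The Trial Summary has a domain called "Weekly Calendars and Safety Monitoring", where adverse events are an entry of their own. Item G6 in section 5.xii.G says: "Weekly Calendars will be used to assess Physical activity, Falls and Injurious Falls". Neither of these two gives a start or end date.

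For the training period, section 5.viii.A says: "After each session, the self-rated walking quality and mental effort visual analogue scales will be recorded". Section 5.viii.B adds that a physiotherapist or clinician watches fatigue and gait and that rest breaks are reported. Section 5.viii.D adds a record of speeds, durations and rests.

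**The concern.** SDTT and SDTT+ differ only during the 12 training sessions. From T1 to T2 both groups are offered the same walking app. If sites start the calendar where section 5.x puts it, prompted collection of falls and injuries begins once treatment has become the same in both arms. While treatment differs, it depends on what participants volunteer or staff notice.

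This affects more than safety reporting. Analysis 2a lists falls among the secondary clinical outcomes at T1 and gives the diary as the source. The T1 diary belongs to the post-training phase, so that outcome would describe about a week after training and nothing during it. Events that were not collected during training cannot be recovered at the analysis stage.

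**Working it through.** The protocol states no figure that could be reproduced here. The check sets each collection tool against its time window and content.

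| Tool (section) | Window | Falls or injuries | Muscle pain | Fatigue |
|---|---|---|---|---|
| Weekly calendar (5.x.B; Trial Summary; G6) | T1 to T2 in 5.x; no window elsewhere | Yes | No | Yes (5.x.B and Summary) |
| Home diary (5.vii.B, 5.ix.B, 5.xi.B) | Seven days at T0, T1, T2 | Falls | No | Yes |
| Post-session visual analogue scales (5.viii.A) | Each session | No | No | No |
| Staff observation and break log (5.viii.B) | Each session | No | No | Yes |
| Training record (5.viii.D) | Each session | No | No | No |
| Pain scale (B7) | T0, T1, T2 | No | General pain only | No |
| FACIT Fatigue (B6) | T0, T1, T2; past week | No | No | Yes |
| Fall record (B1) | 12 months back at T0; then whole trial, no instrument named | Yes | No | No |
| Adverse event form (5.xiii) | Whole trial, on site awareness | Not prompted; form not shown | Not prompted; form not shown | Not prompted; form not shown |

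*Does a diary run during training?* Section 5.iv places the T1 functional assessment within 2 days of the last training visit. The T1 home assessment is in the same post-training phase and starts no later than 5 days after that assessment. The T0 diary belongs to the pre-training phase. So none runs during training.

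*What remains between T0 and T1?* For fatigue, staff observation at each session, plus FACIT at T1, which looks back one week. For falls, injuries and myalgia, only the adverse event form, and B1 without an instrument.

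*Scale, as an illustration.* Inputs: 70% of people with PD fall each year (section 3), 126 participants, and training of 2 to 6 weeks (section 5.i). Assume a constant hazard:

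- Weekly hazard: h = −ln(1 − 0.70)/52 = 1.204/52 = 0.0232.
- Probability of at least one fall in w weeks: P(w) = 1 − exp(−h·w) = 1 − 0.30^(w/52).
- w = 2: P = 4.5%; 126 × 0.0453 = 5.7 participants.
- w = 6: P = 13.0%; 126 × 0.1297 = 16.3 participants.

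*Share of follow-up time.* The post-training phase lasts 14 days and T2 comes 12 weeks after its completion (section 5.iv), so T1 to T2 is about 2 + 12 = 14 weeks. Training is then 2/(2 + 14) = 12.5% to 6/(6 + 14) = 30% of training plus T1 to T2.

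Six weeks may not be the upper limit. Section 5.iv allows 0 to 4 days between sessions, so 12 sessions could span 12 + 11 × 4 = 56 days, or 8 weeks. P(8) is 16.9%, or about 21 participants.

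**The case against.** The strongest reply is that the intent is clear and only the scheduling text is loose. Section 5.xiii and B1 both commit to recording falls throughout, and the Trial Summary and G6 put no window on the calendar. A start after training is thus inferred from the section in which the calendar is described. Participants are also seen at 12 supervised visits no more than 4 days apart, and the adverse event form must be returned within 24 hours of awareness. The content of that form and of the session records is not shown, so a myalgia prompt on one of them cannot be excluded. All of this stands. It makes the calendar's start unclear rather than certainly late. It does not supply a scheduled prompt: a site following section 5.x would start the calendar at T1, and nothing listed for the sessions asks about falls, injuries or muscle pain since the last visit.

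A reader might infer more than the protocol supports:

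- *That no harms are actively collected in training.* Fatigue is, at every session; FACIT and the pain scale follow at T1.
- *That events other than falls are never asked about.* The odd calendar entry on falls and adverse events is probably a lost separator, since the Trial Summary lists adverse events and then falls and injuries in the same order. Health services use is in both lists.
- *That sites learn of events only by chance.* Frequent supervised contact makes that too strong.
- *That the trial fails a comparative safety aim.* Section 4 states no such objective or endpoint.

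**Conclusion.** The point holds in a limited form. The protocol promises whole-trial monitoring of four named harms. For falls and injuries, its only ongoing prompted tool is scheduled only from T1 to T2, and the sections disagree on whether that window is meant. For myalgia, no listed tool names it at any time. During training these three harms therefore appear to rest on passive reporting, and the diary-based falls outcome at T1 does not cover training. Fatigue is adequately covered.

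The period concerned is 12.5% to 30% of training plus T1 to T2, and it is the whole of the time in which assigned treatment differs. The estimate of about 6 to 16 participants falling in it is an order of magnitude only. It assumes a constant hazard and applies a general PD figure to a sample screened to Hoehn and Yahr I to III. Nor are these falls necessarily lost: some would reach staff at sessions. The verdict also assumes that forms not shown contain no relevant prompts. It matters because this is data collection, which a later analysis document cannot repair.

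**What to change.** - State in section 5.x, G6 and the Trial Summary that the weekly calendar starts at T0 and runs without a break to T2.
- Add a muscle-pain item to the calendar, and list adverse events as a separate entry, as the Trial Summary does.
- At each training session, next to the existing scales, ask one standard question in both arms: any fall, injury, muscle pain or other health event since the last session?
- Name the instrument for falls after T0 in B1. In analysis 2a, either take falls up to T1 from the calendar or state that the diary outcome covers only the post-training week.
- Reconcile the Trial Summary and sections 5.x.B, 5.xii.B (B1), 5.xii.G (G6), 5.xiii and 6.vi with these changes.

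The cost is protocol wording, one added calendar item and one separated entry, 2 to 6 more calendar weeks per participant (plus any gap between T0 and the first session), and about a minute at visits that already take place.
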